**2019**

## ABSTRACT

The aim of this project is to characterize the effects of two types of exercise – isometric versus isotonic – on shoulder pain and function and the relationship with neuromuscular control in individuals with rotator cuff (RC) tendinopathy. Forty-six individuals (18-60 years old) with shoulder pain (>3 months) and proven unilateral tendinopathy in the supraspinatus and/or infraspinatus by means of ultrasound or magnetic resonance imaging will participate in this study. Subjects will be randomly allocated to one of two exercise groups: isometric and isotonic. They will be evaluated before and after the first treatment session, and again after six weeks of treatment. The outcomes to be evaluated are: a) pain and general shoulder function, using the Penn Shoulder Score and The Western Ontario Rotator Cuff Index questionnaire; b) neuromuscular control through the electromyographic activity of the trapezius (lower portion), serratus anterior, deltoid (middle portion), and infraspinatus, during maximal isometric contractions of shoulder elevation at 90°, internal and external rotation of the shoulder at 0° of arm elevation and during elevation of the arm at 30, 60, 90 and 120 degrees with and without load using a surface electromyographic signal recording system (EMG system do Brazil®); we will evaluate the amplitude of muscular activity of each muscle and the ratio between muscle pairs: 1) infraspinatus and middle deltoid; 2) infraspinatus and lower trapezius; and 3) lower trapezius and serratus anterior; and c) functional performance through tests that simulate activities of daily living, which include: reaching a point above the head; reach the back of the head; and reaching the back or the opposite scapula, where the performance time and levels of pain and effort will be evaluated. The two groups will undergo a protocol of stretching and strengthening of the periscapular musculature. The isometric group will perform additional exercises for the RC, with 3 repetitions of 32s at 70% of the maximum isometric force for each exercise. The isotonic group will perform exercises for RC in a concentric and eccentric way, with 3 sets of 8 repetitions for each exercise at 8 RM. The exercise load of the two groups will be adjusted in weeks 3 and 5 of the six-week protocol. Treatment effects between groups will be evaluated using two-way ANOVAs with repeated measures, with the aid of the Statistical Package for the Social Sciences (SPSS) software. The results of this study will contribute to knowledge in the field of assessment and rehabilitation of the shoulder complex and may support decision-making process for treating RC tendinopathy.

**Keywords:** Pain management, exercise therapy, electromyography, subacromial impingement syndrome.

## 1 Introduction

Shoulder pain is a common problem, being the third most frequent cause of musculoskeletal complaints (1). The dysfunctions that affect the shoulder can be characterized by limitations of range of motion due to pain and restrictions in activities of daily living, reducing functional independence and affecting the quality of life of affected individuals (2). Among the most common causes of shoulder pain is rotator cuff (RC) dysfunction, which consists of tendinopathy of one or more of the four RC muscles, which can progress to partial or total rupture of its tendons, associated or not with inflammation of shoulder bursae (3,4).

Effective shoulder movement and function is achieved through a combined effort of the scapula stabilizing muscles, deltoid, RC muscles, as well as the latissimus dorsi and pectoralis major (4). However, it is known the coordinated activity of the RC muscles (supraspinatus, infraspinatus, teres minor and subscapularis) is responsible for mechanical stability of the glenohumeral joint through stabilization or compression of the humeral head within the glenoid fossa during shoulder movements. (3,4).

Multiple factors may contribute to the development of RC tendinopathy, which are classified as: extrinsic, which originate externally to the tendons causing compression or shear to them, due to anatomical and biomechanical changes; and the intrinsic factors, which originate due to alterations in the mechanical, morphological and vascular properties of the tendons, as well as genetic predisposition (5,4). Both factors may be related and be potentiated with age and excessive mechanical load (5,6,3,4).

RC tendinopathy, related to subacromial impingement syndrome, has been associated with changes in motor control, since it is well described in the literature that there are changes in scapular kinematics during arm elevation, such as a reduction in posterior tilt and upward rotation and increase in the internal rotation of the scapula in individuals with subacromial impingement (7,8). In association with the movements, an altered activation of the periscapular musculature is verified during arm elevation, such as a decrease in the activation of the serratus anterior and the middle and lower portions of the trapezius (9,10), and an increase in the activation of the upper portion of the trapezius (11, 12,2,9). In addition, failure in the coordination between the lower trapezius and the

serratus anterior and between the upper and lower portions of the trapezius is verified, evidenced by the alteration of the activation ratio between these muscles (13).

Regarding the activation of RC muscles, there is reduced co-activation of RC and increased activation of the middle deltoid at the beginning of humeral elevation (14) and of the posterior deltoid, when the RC is fatigued, injured or ruptured, as a compensation to avoid reduction of the arm elevation movement and stabilize the glenohumeral joint(15,16). This imbalance between RC and deltoid activation may contribute to excessive superior translation of the humeral head (17) and, thus, greater risk for developing subacromial impingement syndrome and RC disease.

Although these muscle and movement changes are verified, there is little evidence to support whether these changes are caused by pain arising from the clinical condition or whether the pain is from the cumulative effect of changes in muscle activation and movement. Furthermore, the cause of local pain in tendinopathy remains elusive, as the level of pain varies substantially and is not always related to local pathology, suggesting a central sensitization in individuals with RC tendinopathy (3). Thus, in addition to focusing on interventions that reduce the risk of subacromial impingement, it is important to focus on interventions aimed at improving pain, in order to investigate the relationship between the clinical condition, pain and neuromuscular coordination in these individuals.

A primary intervention to treat RC tendinopathy is active therapeutic exercise (3), which has provided similar results to those who underwent surgical interventions, but with additional benefits of exercise, which are: less absenteeism, quick return to work and reduced cost to the health systems (18). Many exercise strategies have been proposed, however, uncertainty persists regarding the most effective one to treat the pain, weakness and loss of function associated with RC tendinopathy (3). However, pain reduction is a priority (3) and exercises with mechanical load, which stimulate tendon healing responses, accelerate the metabolism of tenocytes and tissue repair (19,20).

In this sense, resistance training in general, including isometric and isotonic exercises, focusing on both RC and scapular stabilizer muscles, in

patients with RC tendinopathy and subacromial impingement syndrome, has been shown to be effective in improving pain and function. (21). Comparison of isolated eccentric or concentric exercise interventions found no difference in efficacy, with both resulting in improvements in function, range of motion, and strength (22). Regarding isometric contractions, there is evidence that they help control pain when used in lower limb tendinopathies, but there is still no conclusive evidence about their effects on RC tendinopathies (23).

High load isotonic exercises have been shown to be effective for rehabilitation of lower limb tendinopathies, such as patellar tendinopathy (24) and Achilles tendinopathy (25). However, in recent years, isometric exercises have emerged as an excellent tool for tendinopathy rehabilitation (26–30). Isometric exercises have been shown to be more effective for quadriceps pain and function, both with short and long contraction durations (26), and more effective for reducing pain, increasing strength, and reducing cortical inhibition when compared with isotonic exercise, immediately (27) and after 4 weeks (28) when used in the treatment of patellar tendinopathy. Furthermore, submaximal isometric exercise has been shown to increase pressure pain threshold, reduce heat pain perception and reduce pain temporal summation in men and women (29). Applied to RC tendinopathy, we currently have data from a pilot study (30), which suggests that low-load isometric exercises for RC tendinopathy may positively influence pain and tendon stiffness.

Although these studies indicate positive effects of isometric exercises on pain, function and reduction of cortical inhibition in individuals with tendinopathy, to our knowledge, no studies have evaluated the effects of an isometric RC strengthening program on pain, function and neuromuscular control among RC muscles and periscapular and deltoid muscles during the arm raise task compared to an isotonic RC strengthening program. Thus, the aim of this study is to verify the effects of isometric exercise, applied to the RC muscles, compared to isotonic exercise, on pain, function and neuromuscular control in individuals with RC tendinopathy.

## **2 Rationale**

RC tendon disease, both symptomatic and asymptomatic, have a high

prevalence in the general population, reaching up to 30% (31). This dysfunction is related to biomechanical factors, life habits and genetic predisposition, and influenced by age and overload to the tendons (5,32). The great clinical relevance of this condition is due to the fact that there is a high risk of progression of the tendinopathy to partial or total rupture of the tendons, causing symptoms of pain, weakness (32), and important functional limitations (33).

Conservative treatment, based on physiotherapeutic intervention, is indicated for treating RC tendinopathies and ruptures (32), especially resistance training which progressively imposes load on the tendon, in order to help in its repair by altering its metabolism and mechanical and structural properties (6). Among the various forms of resistance, eccentric and concentric exercises have been shown to be effective in improving overall shoulder function (22), and few studies (4,30) have been developed evaluating the effects of isometric exercise on RC tendinopathy.

However, isometric exercise has emerged as an important approach to improve pain in tendinopathies (27–29) and, when compared to isotonic exercise, it has been shown to be superior in terms of pain, strength, function in general, as well as in the reduction of cortical inhibition in the treatment of patellar tendinopathy (27). Thus, the rationale is the clinical relevance of evaluating the effects of isometric exercise applied to RC tendinopathy on pain, function and neuromuscular control involved in the shoulder complex. In this context, this study can help in clinical decision-making regarding the best approach to be considered in the treatment of RC tendinopathy.

### **3 Aims**

#### **3.1 Main aim:**

To characterize the effects of two types of exercise – isometric and isotonic – on shoulder pain and function and the relationship with neuromuscular control in individuals with RC tendinopathy.

#### **3.2 Specific aims:**

- To evaluate the repercussions of isometric and isotonic exercises on pain and function in individuals with RC tendinopathy;
- To verify the effects of isometric and isotonic exercises on neuromuscular control of the shoulder complex muscles through electromyographic activity during maximal isometric contractions and on the motor task of arm arm elevation in individuals with RC tendinopathy;
- To analyze the relationship between effects on pain, neuromuscular control, functional performance and function of the shoulder complex;
- To verify the effects of isometric exercise compared to isotonic exercise on the variables described, immediately after an exercise session and after six weeks of intervention in individuals with RC tendinopathy.

### **4 Hypothesis**

According to the positive and superior results presented from the isometric exercise applied to patellar tendinopathy in relation to the isotonic exercise, both immediately and after the period intervention, in pain, strength and function of the quadriceps, we hypothesize that this exercise modality will be superior to the exercise isotonic in individuals with RC tendinopathy, both immediately and after 6 weeks of intervention. We hypothesize that isometric exercise can reduce pain and improve functional performance and neuromuscular control of the shoulder complex, thus resulting in better function in this population.

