## 5.2 Sample

Forty-six individuals with a clinical diagnosis of unilateral tendinopathy of the supraspinatus and/or infraspinatus tendon by means of ultrasonography (US) or nuclear magnetic resonance (NMR) exams, between 18 and 60 years of age, of both sexes will participate in this study. They will be randomly divided and allocated into two exercise groups, with 23 individuals each: 1) isometric group, which will undergo an isometric resistance training protocol for the RC musculature associated with a stretching and strengthening protocol focused on the periscapular musculature; and 2) isotonic group, which will undergo an isotonic resistance training protocol for the RC musculature associated with a stretching and strengthening protocol focused on the periscapular musculature.

Sampling will be non-probabilistic type of consecutive cases, where individuals will be recruited from a waiting list for physiotherapeutic care in the Physical Therapy Department of UFRN and through dissemination carried out at UFRN, in the city of Natal-RN and social media through posters. The sample size was determined considering the main outcome variable, pain with arm elevation without load, considering a difference between means of 2.05 and standard deviation of 2.30 in the numerical pain rating scale (NPRS) (34). Adopting a 80% Power and  $\alpha = 0.05$ , at least 21 individuals per group will be required. Considering possible sample losses of approximately 10%, the sample should be at least 23 individuals per group.

This project will be sent to the Ethics and Research Committee of UFRN (CEP/UFRN), through the registration in Plataforma Brasil, and will only start its activities after approval. All volunteers will receive a verbal and written explanation of the objectives and methodology of the study, as well as its risks and benefits; and those who agree to participate must sign an informed consent form, in accordance with Resolution 466/12 of the National Health Council, confirming their participation in the study. The project will be submitted to the Brazilian Registry of Clinical Trials (<http://www.ensaiosclinicos.gov.br/>) before

starting to recruit individuals.

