## 5.7 Statistical analysis

Data will be analyzed statistically in a descriptive and inferential way. Mean and standard deviation will be calculated for all demographics and dependent variables. Regarding inferential analyses, initially, the Shapiro-Wilk Normality Test will be used to classify the distribution of each variable.

In order to perform the comparison between the two groups (isometric and isotonic) and between the evaluations, for each dependent variable, we will apply two-way ANOVA with repeated measures when the data are considered parametric and Friedman when the data are non-parametric.

When necessary, post hoc Tukey or Duncan tests will be applied, respectively. All tests will be performed using the Statistical Package for Social Sciences – SPSS, version 20.0 software, and the significance level adopted will be  $\alpha \leq 0,05$ .

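### Section 5.7 tests every dependent variable at 0.05 with no hierarchy, and the main outcome, named only in 5.2, has no time point and no deciding ANOVA term

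*Combined protocol and SAP*

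**What the plan says.** Section 4 states the hypothesis for two occasions: "this exercise modality will be superior to the exercise isotonic in individuals with RC tendinopathy, both immediately and after 6 weeks of intervention". Its next sentence extends the expected benefit to pain, functional performance, neuromuscular control and overall function.

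Section 5.7 gives one rule for all outcomes: "for each dependent variable, we will apply two-way ANOVA with repeated measures", with Friedman's test for non-normal data and Tukey or Duncan post hoc tests when needed. One level, 0.05, applies throughout ("the significance level adopted will be" 0.05 or less). The section does not mention a primary outcome, a primary time point, or which term of the ANOVA (group, or group by time) carries the comparison.

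A main outcome is named once, in 5.2: "The sample size was determined considering the main outcome variable, pain with arm elevation without load". No time point is attached. The abstract describes its pain and function outcome as "pain and general shoulder function, using the Penn Shoulder Score and The Western Ontario Rotator Cuff Index questionnaire", and 5.4.1, the section on pain and function assessment, covers the same two questionnaires. The aims, the hypothesis and 5.7 do not name the main outcome. Section 5.4.2 does provide for an NPRS rating after the tests.

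**The concern.** The superiority conclusion in section 4 is not tied to any one result. Followed as written, 5.7 produces a long series of tests of equal standing. If the NPRS comparison were null but an EMG ratio or one task time were significant, nothing in the plan would say that the hypothesis had failed. The main outcome also leaves choices open: the immediate or the six-week result, and the group effect or the interaction. At stake is whether a statement that isometric exercise is superior carries the error rate that a reader would assume from a 0.05 test.

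**Working it through.** **The plan's own figure.** Inputs from 5.2: "considering a difference between means of 2.05 and standard deviation of 2.30 in the numerical pain rating scale (NPRS"), 80% power, alpha 0.05, and "at least 21 individuals per group will be required".

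- Standardised difference: 2.05 / 2.30 = 0.89.
- Normal approximation, two-sided: n = 2 × (1.96 + 0.84)² × (2.30/2.05)² = 19.8, so 20 per group.
- Exact t calculation: 21 per group, power 80.5%. A one-sided test would need only 16 (normal) or 17 (t), so the stated 21 is two-sided.
- Losses: 21 / 0.9 = 23.3. The planned 23 is within one person per group of this and is not at issue.

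The sample size therefore reproduces, for one two-sided comparison of one variable at one time point.

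**Number of variables.** The documents give no list, so this count is a reading of the abstract and of 5.4.1 to 5.4.3:

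| Group | Count |
|---|---|
| EMG amplitude: 4 muscles × (3 maximal contractions + 4 angles × 2 load conditions) | 4 × 11 = 44 |
| EMG ratios: 3 pairs × 11 conditions | 33 |
| Functional tests: 3 tasks × (time, pain, effort) | 9 |
| PSS total, WORC total, NPRS without and with load | 4 |
| Total | 90 |

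**Chance of at least one false positive, one time point, no true effects.** Under independence the formula is 1 − 0.95^m for either direction and 1 − 0.975^m for results favouring isometric only. For a common correlation, the same probability was obtained by integrating over a shared normal factor. With m = 90:

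| Correlation | Either direction (nominal 5%) | Toward isometric only (nominal 2.5%) |
|---|---|---|
| 0 | 99% | 90% |
| 0.5 | 75% | 39% |
| 0.9 | 22% | 11% |

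A single correlation of 0.9 is an extreme case, because it treats EMG, questionnaires and task times as near-duplicates. A simulation with correlation of 0.3 to 0.9 within blocks (each muscle, each ratio, the clinical scores, the functional tests) and 0 to 0.3 between blocks gives 63% to 98% in either direction.

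Leaving EMG out altogether, 9 + 4 = 13 variables give 1 − 0.95^13 = 49% if independent and 33% at correlation 0.5.

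**Main outcome alone, two time points.**

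- Success at either one, two-sided: 1 − 0.95² = 9.75% if independent, and 9.5%, 9.1% and 8.3% at correlations 0.3, 0.5 and 0.7. Toward isometric only, it is 4.8% to 4.2% for correlations 0.3 to 0.7, against 2.5%.
- Success required at both, toward isometric: 0.2% to 0.8% for correlations 0.3 to 0.7 when neither time point has an effect. If one time point has a real effect, it is at most 2.5%.
- Power for both, with the planned effect present at each: between 0.805² = 65% (independent) and 80% (perfectly correlated), at 21 per group.

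**The case against.** The strongest reply is that the plan does have a top outcome. Section 5.2 names it and sizes the trial on it, 5.4.2 provides an NPRS rating, and chance findings on other variables do not inflate that outcome's own error. That is correct. It does not settle the point, because neither the hypothesis nor 5.7 makes that outcome decide the conclusion, and its time point and ANOVA term remain open.

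Several stronger readings are tempting and are not supported:

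- *A chance finding is almost certain.* The documents give neither the number of tests nor their correlation. One muscle at neighbouring angles, and ratios built from the same amplitudes, are likely to be strongly correlated. The defensible range for 90 variables at one time point is 22% to 99%.
- *The count should include questionnaire domains.* Section 5.4.1 defines a total score for PSS and for WORC, and 5.7 does not say that domains are tested separately.
- *Two time points double the false positives.* Section 5.7 runs one ANOVA per variable across all evaluations. One group-by-time interaction covers both follow-ups, and post hoc tests come only when needed.
- *The error toward isometric superiority on the main outcome is 8 to 10%.* That figure is two-sided, and it assumes that either time point suffices. Section 4 says both. Read as a requirement for both, the error falls below nominal and the cost is power.
- *The plan allows any single result to confirm the hypothesis.* Section 4 joins its outcomes with and, so a lone EMG result would not satisfy its wording. What the plan lacks is a rule that excludes such a claim.

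**Conclusion.** The concern holds as a missing decision rule; the sample-size arithmetic is sound. With every dependent variable tested at 0.05 and no hierarchy, the chance of some false positive is well above 5% in every scenario computed for the 90-variable reading, from 22% to 99% in either direction. Toward isometric only, it is 11% to 90% against 2.5%. These figures assume no true effect on any variable, a count inferred from the text, and one contrast per variable at one time point. For the main outcome alone the exposure is modest: about 8 to 10% two-sided if either time point may be claimed. If both are required there is no inflation, but power is 65% to 80% in place of the planned 80%. Either reading needs to be written down.

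**What to change.** In 5.2 and 5.7, and consistently in the abstract and aims:

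1. Name one primary contrast: the between-group difference in NPRS pain with unloaded arm elevation at one stated time point, two-sided 0.05. State the model term or contrast that estimates it, and base the superiority conclusion on it.
2. Test the other time point at 0.05 only if the first is significant (fixed sequence). Six weeks first is one reasonable order. The aims and hypothesis give both occasions equal weight, so the choice is the sponsor's.
3. Label PSS, WORC, functional performance and the EMG variables as secondary or exploratory. Report them with 95% confidence intervals and state that none is sufficient alone for the superiority claim.

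The cost is wording. The sample size stays at 21 per group, 23 with losses. By comparison, splitting alpha equally over the two time points (0.025 each) would need 26 per group, or 26 / 0.9 = 28.9, so 29 with losses. At the planned 21 per group, the power for each time point would then be 71%. The downside of the proposed rule is that an immediate effect (if six weeks is placed first) or an EMG finding could not carry the claim alone. Section 5.2 places registration before recruitment, so the change fits best before that step.
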